### Outcomes

2.11.

The primary outcome of this study is the improvement of depression, anxiety, and stress scores, as assessed by the DASS-21 questionnaire.

The secondary outcomes include the following:

Reduction in serum cortisol and testosterone levels;Improved BMI; andEnhanced knowledge about PCOS, measured using a structured questionnaire from a previously published study.

## Ethical considerations

3.

Ethical approval was received from the Institutional Review Board of North South University (Approval No. 2024/0RNSU/IRBII 002) and is registered with the Japan Registry of Clinical Trials under the ID jRCT2062240073, https://jrct.mhlw.go.jp/en-latest-detail/jRCT2062240073. The research was conducted in accordance with the principles of the Declaration of Helsinki. Prior to enrollment, all participants were thoroughly informed about the study's purpose, potential risks and benefits, and their rights. Voluntary participation and informed consent were obtained from each participant. Strict confidentiality was maintained for all the study participants throughout the study.

All qualitative and quantitative data was securely stored with restricted access. The participants were informed of their rights, including the voluntary nature of their participation and their ability to withdraw at any time without consequence.

## Quantitative analysis

4.

All data analyses will be performed using the IBM SPSS software (version 26.0, IBM Corp., Armonk, NY, USA). Prior to inferential testing, continuous variables will be evaluated for normality using the Shapiro-Wilk test and inspection of Q-Q plots. When data violate normality assumptions, appropriate transformations (e.g., log or square root) will be applied. If transformation fails to achieve normality, then non-parametric alternatives such as the Wilcoxon signed-rank test (within-group comparisons) and Mann–Whitney U test (between-group comparisons) will be used.

DASS-21 subscales (Depression, Anxiety, Stress) will be separately analyzed as secondary/exploratory using appropriate tests based on normality. A Bonferroni correction will be applied to account for multiple comparisons.

Missing data for primary and secondary outcomes will be handled using multiple imputations, incorporating baseline covariates such as age, BMI, baseline DASS-21 scores, and group assignments to generate plausible values under the assumption of missing at random (MAR). This approach reduces bias and maintains statistical power compared with single-imputation methods such as the last observation carried forward (LOCF). To evaluate the robustness of the findings, sensitivity analyses will be performed under different missing-data assumptions (MCAR and MAR).

All quantitative analyses will be conducted according to the intention-to-treat (ITT) principle, including all randomized participants in their originally assigned groups regardless of adherence to the intervention. The study adopts a two-arm parallel design (intervention and control) with a single primary outcome: participants demonstrating improvement from baseline to the endline score of DASS21. Continuous secondary outcomes, including testosterone and cortisol levels, knowledge scores, and BMI, will be analyzed using a two-way analysis of covariance (ANCOVA) with repeated measures, with the group (intervention and control) as a between-subject factor and time (pre- and post-intervention), and the group × time interaction testing whether the effect of time differs by the group. Potential confounding factors will be adjusted for, and a Bonferroni correction will be applied to account for multiple comparisons. Additionally, exploratory subgroup analyses will be conducted to assess the potential effect modification by age, baseline BMI, and baseline symptom severity. All statistical tests will be two-tailed, with the level of significance set at α = 0.05, unless otherwise specified.

This analytical strategy ensures methodological rigor by addressing statistical assumptions, minimizing false-positive findings, and providing a comprehensive assessment of the digital health education intervention's impact on the mental health and physiological outcomes of women with PCOS.

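### A normality check on the raw variables can replace the baseline-adjusted comparison with unadjusted rank tests, at a cost in precision and in the adjusted effect estimate

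*Protocol article*

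**What the plan says.** The Quantitative analysis section of the protocol article sets a three-step rule.

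1. Check: "Prior to inferential testing, continuous variables will be evaluated for normality using the Shapiro-Wilk test and inspection of Q-Q plots".
2. Transform: "When data violate normality assumptions, appropriate transformations (e.g., log or square root) will be applied".
3. Fall back: "If transformation fails to achieve normality, then non-parametric alternatives such as the Wilcoxon signed-rank test (within-group comparisons", and the same sentence goes on to the "Mann–Whitney U test (between-group comparisons) will be used".

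The next paragraph puts the three DASS-21 subscales under the same rule: they "will be separately analyzed as secondary/exploratory using appropriate tests based on normality".

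Three other places bear on this:

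- The Introduction states the hypothesis between groups: a greater reduction in stress, anxiety and depression than under usual treatment.
- Section 2.9 (Sample size and power) assumes that baseline covariates explain 10% of the outcome variance and raises the effect size f from 0.22 to 0.2319 on that ground.
- Later in the Quantitative analysis section, a repeated-measures ANCOVA with a group × time interaction is named for testosterone, cortisol, knowledge and BMI, with the statement "Potential confounding factors will be adjusted for, and a Bonferroni correction will be applied to account for multiple comparisons".

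**The concern.** The rule examines the wrong object. A linear model needs approximate normality, and only weakly, of its residuals. With 212 women randomised, or about 170 after 20% attrition, inference on an arm difference depends little on it.

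The fallback also changes the analysis. Neither rank test takes covariates, so the adjustment built into the sample size disappears and no adjusted effect estimate is produced. For cortisol, testosterone, BMI and knowledge, it would also displace the group × time ANCOVA that the same section names.

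The within-group Wilcoxon test has a further weakness: it compares each arm with its own baseline. Improvement that is significant in the intervention arm but not in the control arm is not evidence of a difference between arms, though it is easily read that way.

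Finally, which test is used would depend on the trial's own endline data, although a fixed choice is available at almost no cost.

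**Working it through.** **The plan's own figure.** f = 0.22/√(1 − 0.10) = 0.2319. Taking the noncentrality as f²N with 1 and N − 2 degrees of freedom and α = 0.05, N = 148 gives power 0.8003. Then 148/(1 − 0.20) = 185. The stated 148 and 185 are therefore reproduced, and they rest on the 10% covariate adjustment.

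**Power with and without the adjustment.** Inputs from the article: d = 0.44, R² = 0.10, two-sided α = 0.05, 148/2 = 74 per arm planned, 106 per arm enrolled, and 106 × 0.80 ≈ 85 per arm after attrition. Normal approximation:

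- adjusted: Φ(d/√(1 − R²) · √(n/2) − 1.96)
- unadjusted: Φ(d · √(n/2) − 1.96)
- Mann–Whitney: as unadjusted, with n multiplied by 0.955 (its relative efficiency under normality)

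At 74 per arm:

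- adjusted: 0.4638 × 6.083 − 1.96 = 0.861, power 80.5%
- unadjusted: 0.44 × 6.083 − 1.96 = 0.716, power 76.3%
- Mann–Whitney: 0.44 × 5.944 − 1.96 = 0.655, power 74.4%

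| Per arm | Adjusted, R² = 0.10 | Unadjusted | Mann–Whitney |
|---|---|---|---|
| 74 | 80.5% | 76.3% | 74.4% |
| 85 | 85.6% | 81.8% | 80.0% |
| 106 | 92.2% | 89.3% | 87.9% |

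**Simulation with a correlated baseline score.** The article gives no subscale mean, SD or shape, so every distribution here is an assumption: integer scores limited to 0–21, a latent baseline–endline correlation of 0.3, 0.5 or 0.7, and a shift of 0.44 latent SD. With a moderately skewed shape (gamma, mean 6, shape 3), 85 per arm and 1,000 runs each:

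| Correlation | ANCOVA | Rank ANCOVA | Mann–Whitney, endline | Mann–Whitney, change |
|---|---|---|---|---|
| 0.3 | 85% | 84% | 80% | 61% |
| 0.5 | 88% | 88% | 80% | 74% |
| 0.7 | 96% | 96% | 81% | 91% |

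Against Mann–Whitney on endline scores, ANCOVA gains about 5 to 15 percentage points. None of these figures allows for the Bonferroni correction.

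**How often the fallback is reached.** The check was taken as Shapiro–Wilk at 5% on endline scores in each arm. It counts as failed when the raw, square-root and log(x + 1) scores each fail in at least one arm. Inspection of Q–Q plots cannot be simulated. Over 85 and 106 per arm, mostly with 500 runs each:

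- strong skew (gamma, mean 4, shape 1.5): 100%
- mild to moderate skew (gamma, mean 8, shape 8; mean 6, shape 3): about 64–97%
- roughly symmetric (rounded normal, mean 8, SD 3.5; mean 10, SD 4): 19–56%

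**No treatment effect.** Both arms improve by 0.25 SD, 106 per arm, moderate skew, 1,000 runs for each correlation. Type I error was 4.7–5.5% for ANCOVA despite the skew, and 4.0–5.6% for Mann–Whitney on endline or change scores. The paired Wilcoxon tests were significant in the intervention arm only in 24.9%, 21.4% and 11.5% of trials at correlations 0.3, 0.5 and 0.7. If p is the chance that one arm is significant, this rate is p(1 − p). It cannot exceed 25%, reached at p = 0.5, and it falls as p moves towards 0 or 1.

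**The case against.** The strongest defence is that the fallback includes a valid between-group test. A reader who stops at the Wilcoxon test might infer that the rank analyses do not test the trial's hypothesis. The text does not support that: the same sentence names Mann–Whitney for comparisons between groups, and that test held its error rate. The loss is in precision. At 106 per arm it still has about 88% power, and at 85 about 80%, which is the planned level. This stands.

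A reader might also infer that DASS-21 scores are bound to be skewed and so bound to reach the rank tests. The article reports no distribution, and transformation and Q–Q plots come first. The range of 19% to 100% shows how far the answer depends on the assumed shape. This stands too.

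Three further limits apply:

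- The group × time ANCOVA is not listed for the subscales. For them, the lost adjustment is relative to Section 2.9.
- The same section describes a single primary outcome as participants showing improvement on the DASS-21. If that means a proportion, the normality rule does not reach it. Section 2.11, however, makes the depression, anxiety and stress scores the primary outcome, so the subscales cannot be treated as marginal.
- Nothing in the article says that within-group results will be read as treatment effects. The 12–25% arises only if they are. The rate for significance in exactly one arm, 24–49%, includes the control-only direction and lies near its ceiling of 50% at the upper end.

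None of this answers the main point: the rule tests variables rather than residuals, and both named fallbacks drop the adjustment.

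**Conclusion.** The point holds as a matter of precision and pre-specification. It does not show that the planned between-group test is invalid. If the fallback is reached, the cost at d = 0.44 is about 6 points of power at the planned 74 per arm (80.5% to 74.4%), which takes it below the 80% target. At 85 per arm it is about 5 to 15 points against ANCOVA on the baseline score, under assumed correlations of 0.3 to 0.7. An adjusted effect estimate is lost as well. Only the within-group Wilcoxon test fails to address the hypothesis.

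The analytic figures rest on the article's d and R² and a normal approximation. The simulated ones rest on assumed score distributions. The chance of reaching the fallback cannot be fixed from the article, so confidence in the defect is high, and in its practical size moderate. It should be corrected, because the better analysis uses data already being collected and the Results section says that analysis has not started.

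**What to change.** Before analysis starts, replace the normality rule with a fixed analysis:

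- For each continuous outcome, including the DASS-21 scores, estimate one between-arm difference at endline by ANCOVA adjusted for the baseline score, whatever Shapiro–Wilk shows.
- Check the residuals of that model, and use heteroscedasticity-robust or bootstrap standard errors.
- Keep a rank-based ANCOVA as a sensitivity analysis. In the simulation it lost almost nothing (84/88/96% against 85/88/96%).
- Label any within-group test as descriptive, and state that it is no evidence of a treatment effect.

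Date the change and record that it preceded any analysis of endline data. The cost is a few sentences in the analysis plan and a little more analysis work. No further data are needed.

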### Sample size and power

2.9.

The sample size was calculated using G* power (version 3.1) for a repeated-measures analysis of variance (ANOVA) with a within-between interaction (F tests). The following parameters were used: two groups, two measurements, non-sphericity correction ε = 1.0, α = 0.05 (Type I error), and power = 0.80 (Type II error = 0.20).

The effect size f = 0.2319 was derived based on prior literature and our study design. Specifically, a previous study reported a Cohen's d of 0.44 [31] for similar outcomes. In our two-group repeated-measures design, the corresponding unadjusted effect size was calculated as follows:

f=d/2=0.44/2=0.22.

We planned to adjust for baseline covariates in the analysis. Assuming that covariates explain 10% of the variance in the outcome (ρ² = 0.10), the adjusted effect size is as follows:

$${\text{f}}_{\text{adj}}=0.22/\surd 1-0.10=0.2319.$$

Using these parameters in G*Power (F tests, repeated-measures ANOVA, within–between interaction), the calculated total sample size required to detect the prespecified effect size with 80% [32] power at α = 0.05 was 148 participants. To account for an expected 20% [33] attrition rate, the sample size was inflated as follows:

$${\text{N}}_{\text{adjusted}}=148/1-0.20=185.$$

Thus, the final recruitment target was 185 participants (93 in the intervention group and 92 in the control group) to ensure sufficient power for the primary analysis.

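### Low-severity improvement: Holm's step-down procedure could replace the two single-step Bonferroni corrections, with the same 5% family-wise control and some extra power

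*Protocol article*

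**What the plan says.** All references are to the protocol article. Quantitative analysis (section 4) names Bonferroni twice.

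- On the subscales: "DASS-21 subscales (Depression, Anxiety, Stress) will be separately analyzed as secondary/exploratory using appropriate tests based on normality". The next sentence is "A Bonferroni correction will be applied to account for multiple comparisons".
- On the other endpoints, the section sets out a repeated-measures ANCOVA for "Continuous secondary outcomes, including testosterone and cortisol levels, knowledge scores, and BMI", and then states: "Potential confounding factors will be adjusted for, and a Bonferroni correction will be applied to account for multiple comparisons".

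The same section describes a design "with a single primary outcome: participants demonstrating improvement from baseline to the endline score of DASS21", and sets the general level: "All statistical tests will be two-tailed, with the level of significance set at α = 0.05, unless otherwise specified". It names no stepwise procedure and gives no reason for the single-step version. Neither the number of tests nor the members of each family is stated.

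Outcomes (section 2.11) differs on status. It lists improvement in the depression, anxiety and stress scores as the primary outcome, whereas section 4 treats the subscales as secondary or exploratory.

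**The concern.** Single-step Bonferroni compares every p value with 0.05/m, where m is the family size. Holm compares the smallest p value with 0.05/m, the next with 0.05/(m-1), and so on up to 0.05, stopping at the first failure. Its first threshold equals Bonferroni's and the later ones are more lenient, so it cannot reject less. It needs no assumption about correlation to hold the family-wise error at 5%.

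The trial hypothesises (Introduction) that stress, anxiety and depression will all fall. That is the setting in which several rejections are expected and in which a single-step correction gives up power. At stake is some avoidable loss of power on secondary and exploratory tests. Validity is not at stake.

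**Working it through.** **The plan's own figure.** Sample size and power (section 2.9) gives f = 0.44/2 = 0.22, adjusted to 0.22/√(1 - 0.10) = 0.2319, and N = 148. With noncentral F, df 1 and N - 2, and noncentrality f²N = 0.2319² × 148 = 7.96, power at α = 0.05 is 0.8003. N = 148 is reproduced, and 148/(1 - 0.20) = 185. These figures use an uncorrected α of 0.05, so the choice between Bonferroni and Holm does not affect them.

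**Inputs from the document.** d = 0.44 and 20% attrition (section 2.9); 106 enrolled per arm (section 10); two-sided 5% (section 4). Completers per arm: 106 × 0.80 = 84.8, taken as 85.

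**Assumptions, because the document does not give them.** Family sizes of 3 (subscales) and 4 (testosterone, cortisol, knowledge, BMI); d = 0.44 on every outcome in the family; common correlation from 0 to 0.8; z tests.

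**Thresholds.** For m = 3, Bonferroni uses 0.0167 throughout and Holm uses 0.0167, 0.025, 0.05. For m = 4, Bonferroni uses 0.0125 throughout and Holm uses 0.0125, 0.0167, 0.025, 0.05.

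**Bonferroni power in closed form.** The mean of z is 0.44 × √(85/2) = 2.868. For m = 3 the critical value is 2.394, so power = Φ(2.868 - 2.394) = 0.68. For m = 4 it is 2.498, so power = Φ(2.868 - 2.498) = 0.64.

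**Power per outcome by simulation** (200,000 trials per row, 85 per arm; simulation error about 0.001):

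| Correlation | m = 3 Bonferroni | m = 3 Holm | m = 4 Bonferroni | m = 4 Holm |
|---|---|---|---|---|
| 0 | 0.683 | 0.774 | 0.645 | 0.753 |
| 0.3 | 0.684 | 0.766 | 0.645 | 0.742 |
| 0.5 | 0.684 | 0.759 | 0.645 | 0.734 |
| 0.7 | 0.684 | 0.753 | 0.645 | 0.726 |
| 0.8 | 0.683 | 0.746 | 0.645 | 0.721 |

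The gain falls from about 9 to 6 points for m = 3, and from about 11 to 8 for m = 4, as correlation rises.

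**What does not change.** Power for at least one rejection is the same under both methods (m = 3: 0.97 at correlation 0, 0.84 at 0.7). No simulated trial lost a Bonferroni rejection under Holm.

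**Only one real effect.** At correlation 0.5, power for that outcome is 0.680 against 0.681 for m = 3, and 0.645 under both for m = 4. The gain is negligible.

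**Family-wise error, m = 3.** With no real effect anywhere, both methods give 0.049 at correlation 0 and 0.040 at 0.7. With two real effects and one true null (correlation 0.5), the figures are 0.017 for Bonferroni and 0.036 for Holm. All are below 0.05.

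**The case against.** The strongest reply is that nothing is wrong here. Bonferroni is valid, prespecified and conservative, and simultaneous confidence intervals follow from it directly. The corrected tests are secondary or exploratory under section 4, the single primary outcome carries no correction, and the families are a reader's inference: the list of secondary outcomes opens with an inclusive word, and the second correction might refer to comparisons within a model. Section 2.9 cites d = 0.44 for similar outcomes in one previous study, which does not support it for hormones, BMI or knowledge. All of this stands. It fixes the severity as low and makes the sizes conditional. It does not remove Holm's dominance for hypothesis testing.

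Two stronger readings are tempting and are not supported.

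- A reader might infer that Bonferroni costs most because the subscales are strongly related. The reverse holds: Holm makes no use of correlation, and its advantage shrinks as correlation rises. Real effects on several outcomes are what favour it.
- A reader might infer that under Bonferroni a true effect on all three subscales would more likely be missed than shown. At 85 per arm and d = 0.44, all-three power is 0.40 to 0.48 for correlation 0.3 to 0.6, but 0.51 at 0.7 and 0.54 at 0.8. It is also 0.54 at correlation 0.6 with the plan's adjusted effect (d = 2 × 0.2319 = 0.4638), and 0.56 to 0.62 for correlation 0.3 to 0.6 with all 106 per arm. The document gives no correlations. Moreover, a claim that required all three to be significant would need no multiplicity correction.

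**Conclusion.** The point holds as a cheap efficiency improvement, not as an error or a contradiction in the choice of correction. The general result, that Holm rejects at least what Bonferroni rejects at the same family-wise 5%, needs none of the numerical assumptions. The size does: 6 to 9 points of power per outcome for three outcomes and 8 to 11 for four, if every outcome in the family has d = 0.44 and 85 per arm complete. The four-outcome figure is the weaker one, because its effect size is only an assumption. The primary analysis, the 148 and 185 of section 2.9 and the 212 enrolled are unaffected.

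The disagreement between sections 2.11 and 4 on the status of the subscales comes first. Until it is settled, the family to be corrected is not defined under either method.

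**What to change.** Section 10 reports that data analysis has not begun, so a dated change can still be prespecified.

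1. Reconcile sections 2.11 and 4 on whether the depression, anxiety and stress scores are primary or secondary/exploratory.
2. Replace Bonferroni by Holm at both places in section 4, naming two families, each at two-sided 5%: {Depression, Anxiety, Stress} and {testosterone, cortisol, BMI, knowledge}.
3. Report unadjusted 95% confidence intervals beside the Holm-adjusted p values, labelled as unadjusted.

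The cost is a few sentences. Holm-adjusted p values follow from the ordinary p values by simple arithmetic, so the planned software is no obstacle. The one real downside is that no simple simultaneous confidence intervals match Holm, so an unadjusted interval may exclude zero where the adjusted test does not reject.

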### Adherence to intervention

2.7.

The study maintained monthly follow-ups, during which the lead researcher contacted the participants in the intervention group. This regular engagement supported the participant's adherence to the intervention. Additionally, if a participant missed a scheduled reminder call from the researcher, the research assistants followed up with supplementary calls to ensure continued participation and compliance.

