## Attrition and post randomization bias

6.

Both groups continued to receive routine gynecological care from their attending physicians throughout the study period. The intervention group received additional support through the smartphone-based digital health education program and bi-monthly follow-up calls. The control group only received standard gynecological management but was counselled by research assistants to return for follow-up after 6 months. Although the frequency of physician follow-up in the control group varied, both groups maintained regular contact within the healthcare system to reduce differential attrition.

The frequency of gynecological follow-up in the control group was not standardized and may have varied among participants, which could influence the adherence or outcome assessments. However, efforts were made to reduce attrition bias by counselling all the control group participants to attend a 6-month follow-up and by maintaining an intention-to-treat analysis in data interpretation.

Although an intention-to-treat analysis and data imputation will be employed to minimize attrition-related bias, differences in dropout rates between the intervention and control groups may still introduce post-randomization bias. Future studies could reduce this risk by incorporating balanced engagement strategies for both groups.

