## Missing data

8.

Efforts to minimize missing data will include thorough training of the study's personnel, regular data monitoring, and timely follow-ups with the participants to ensure complete and accurate data collection. Missing data for primary and secondary outcomes will be handled using multiple imputation methods, thereby incorporating baseline covariates (e.g., age, BMI, baseline DASS-21 scores, and group assignment) to generate plausible values under the assumption of missing at random (MAR). This approach minimizes bias and preserves statistical power compared with single imputation techniques such as last observation carried forward (LOCF). Sensitivity analyses will be conducted under alternative assumptions of MCAR and MAR to evaluate the robustness of the findings. The DASS-21 will be administered only at baseline and at the endline assessment, and no repeated measures will be collected during the intervention period.

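### The missing-data sensitivity analyses (MCAR and MAR) contain nothing weaker than the main MAR assumption, so they cannot show whether the DASS-21 result is robust to outcome-dependent dropout

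*Protocol article*

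**What the plan says.** Section 4 (Quantitative analysis) handles missing primary and secondary outcomes by multiple imputation, to "generate plausible values under the assumption of missing at random (MAR"), with an imputation model "incorporating baseline covariates such as age, BMI, baseline DASS-21 scores, and group assignments". On robustness it says that "sensitivity analyses will be performed under different missing-data assumptions (MCAR and MAR"). Section 8 (Missing data) repeats the plan: "Sensitivity analyses will be conducted under alternative assumptions of MCAR and MAR to evaluate the robustness of the findings". The same section states that "The DASS-21 will be administered only at baseline and at the endline assessment".

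Section 2.9 plans for 20% attrition overall and gives no rates by arm. Section 6 (Attrition and post randomization bias) accepts that, even with intention-to-treat and imputation, "differences in dropout rates between the intervention and control groups may still introduce post-randomization bias". On contact during the trial, section 2.7 has the lead researcher calling the intervention group, and when a call was missed "the research assistants followed up with supplementary calls to ensure continued participation and compliance". Section 6 says of the controls that "The frequency of gynecological follow-up in the control group was not standardized", and that they were counselled to come back at 6 months.

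**The concern.** A sensitivity analysis is useful when it lets the doubtful assumption fail. Here that assumption is MAR: given the baseline covariates and arm, women without an endline DASS-21 would have scored like those with one. The observed data cannot test this. The plan compares MAR with itself and with MCAR, which assumes more. If women leave because of how they feel at the end, both analyses are wrong in the same way and will still agree. The article would then report the finding as robust, which the comparison cannot establish.

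The design sharpens the problem. With no intermediate DASS-21, a woman who drops out contributes no post-baseline score, and MAR rests on baseline variables and arm alone. Section 6 acknowledges that bias may remain after imputation, but no planned analysis shows how large it would have to be to change the conclusion.

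**Working it through.** **1. The plan's own figures.** Section 2.9 gives d = 0.44, f = 0.44/2 = 0.22, and f_adj = 0.22/√0.90 = 0.2319. A noncentral F test with df = (1, N − 2) and noncentrality f²N reaches power 0.8003 at N = 148, and 148/0.80 = 185. Both stated totals reproduce. They matter here only as the source of 0.44 and 20%.

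**2. Strength of the assumptions.** MCAR: missingness is unrelated to any data. MAR: missingness may depend on observed data, here baseline and arm. MNAR: missingness may also depend on the unseen endline score. MCAR implies MAR. The named set therefore holds the main assumption and one stricter than it.

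**3. Do the two planned analyses differ in this design?** This was simulated. Assumptions not in the article: outcome SD = 1, baseline–endline correlation 0.5, 106 per arm (section 10), 20% missing per arm, no true effect, and dropout depending on the unseen endline score in the intervention arm only. The article does not define the MCAR analysis, so it is taken as completers adjusted for baseline. A negative bias favours the intervention. There were 800 runs per scenario.

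| Dropouts worse than completers by | Analysis | Bias (SD) | Rejections at 5% |
|---|---|---|---|
| 0.67 SD | Completers (MCAR) | −0.138 | 18.9% |
| 0.67 SD | MI under MAR | −0.138 | 18.9% |
| 0.67 SD | MI with matching delta | −0.005 | 6.6% |
| 1.06 SD | Completers (MCAR) | −0.211 | 39.1% |
| 1.06 SD | MI under MAR | −0.212 | 37.9% |
| 1.06 SD | MI with matching delta | 0.002 | 5.0% |

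The two planned analyses agree to within 0.001 SD while both are biased.

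**4. Unequal dropout rates alone.** With 30% missing in one arm and 10% in the other, unrelated to outcome, both methods have a bias of 0.003 SD and 5.5% rejections (600 runs). Arm is in the imputation model, so a difference in rates is not by itself a departure from MAR.

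**5. Size of the shift.** Higher DASS-21 is worse. Let p be the proportion missing and δ the amount, in SD, by which dropouts are worse than MAR assumes. The benefit changes by −(p_int × δ_int − p_con × δ_con).

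- 20% missing in each arm, δ = 0.5 in the intervention arm only: 0.20 × 0.5 = 0.10, so 0.44 becomes 0.34. This is 0.10/0.44 = 23% of the planning effect.
- Same rates, δ = 0.5 in the control arm only: 0.44 becomes 0.54.
- Same rates, δ = 0.5 in both arms: the shifts cancel and 0.44 stays 0.44.
- 10% missing in the intervention arm, 30% in the control arm, δ = 0.5 in both: (0.30 − 0.10) × 0.5 = 0.10, so 0.44 becomes 0.54. MAR would understate the benefit.
- 30% missing in the intervention arm, 10% in the control arm, δ = 0.5 in both: 0.44 becomes 0.34.

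**6. Tipping point, δ in the intervention arm only.** Evaluable: 212 × 0.80 = 169.6, about 170. Unadjusted SE = 2/√170 = 0.153 and critical difference = 1.96 × SE = 0.301.

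- Estimate 0.44: (0.44 − 0.301)/0.20 = 0.695, about 0.7 SD.
- Estimate 0.35: (0.35 − 0.301)/0.20 = 0.245, about 0.24 SD from unrounded inputs.

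The SE is held fixed as δ changes, so these values are approximate.

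**The case against.** The strongest reply is that the article gives no evidence of outcome-dependent dropout. It expects 20% attrition overall, says only that differing dropout rates may bias the result, and states that both groups stayed in contact with the healthcare system. It openly discloses residual bias and does not claim that its checks remove it. All of that stands.

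A reader might infer three stronger things, and the article supports none of them.

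- *That it expects informative, arm-dependent dropout.* It acknowledges a possible bias and does not forecast such a mechanism.
- *That the intervention-only calls show MAR will fail.* They may produce unequal rates, but step 4 shows that unequal rates unrelated to outcome do no harm when arm is in the imputation model.
- *That the bias favours the intervention.* Step 5 shows either direction, and heavier control dropout with a common worsening makes MAR understate the benefit.

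It is also fair to say that no analysis detects MNAR from observed data, and delta adjustment does not either. It shows how far MAR must fail before the conclusion changes, which the MCAR/MAR comparison cannot show.

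A last defence would leave the matter to a separate analysis plan. It fails because the article itself names the sensitivity set, twice, and offers it as the evaluation of robustness.

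**Conclusion.** The point holds in a limited form. The stated sensitivity set contains nothing weaker than the main assumption, and in a two-visit design its two members will nearly coincide, so their agreement is not evidence of robustness to outcome-dependent dropout. Whether such dropout occurs, and in which direction it would bias the result, is not known from the article.

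Confidence in the logical point is high. The figures are illustrations, because the article supplies no outcome SD, baseline–endline correlation or attrition by arm. They also apply to a continuous score. Section 2.11 describes the primary outcome as improvement in scores, whereas section 4 speaks of participants who improve. If a proportion is analysed, the SD figures do not carry over directly, though the point about the assumptions does. The change should be made, and it does not call the choice of MAR imputation as the main analysis into question.

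**What to change.** Keep multiple imputation under MAR as the primary handling. In sections 4 and 8, replace or supplement the MCAR/MAR comparison with a delta-adjusted (pattern-mixture) imputation of endline DASS-21:

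- Add δ to the imputed scores over a stated grid, for example 0 to 1 SD.
- Vary δ in the intervention arm alone, in the control arm alone, and in both arms. A common δ alone is not enough, because it cancels when the two arms lose the same share of participants.
- Report the treatment difference with its confidence interval at each grid point, and the tipping point at which the conclusion changes.
- If the primary outcome is a proportion improved, derive improvement from the shifted scores.

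Specify this before analysis starts. Section 10 reports that endline collection began in November 2025 and that analysis had not started, so on the article's account it can still be prespecified. The cost is a few extra imputation runs and one table, with no new data collection.
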